## Background

Schizophrenia is a major severe mental disorder that has profound adverse effects on individuals and poses huge disease burden to families [1]. It usually has an onset in early adulthood and is often accompanied with persistent or relapsing symptoms. According to the estimation of the Global Burden of Disease Study, globally, schizophrenia accounted for 6.51 million DALYs in 2017, representing 0.51% of the all-cause DALYs [2]. Despite its low prevalence, the mortality rate of people with schizophrenia is two to three times higher than that in the general population [3]. And most people with schizophrenia have difficulties with work and social participation. In China, 6 million individuals suffer from schizophrenia: 80% of them with moderate to severe disability; 40% of them have never received treatment [4, 5]. Such high risk of disability among schizophrenic patients and consequent adverse outcomes, which are likely due to extremely low access to psychiatric services, has made schizophrenia a priority public concern in recent years.

International consensus shows that community-based rehabilitation (CBR) service, as a broader supportive approach, is an effective way to improve functioning and negative symptoms and address the treatment gap for schizophrenia [6]. In particular, the WHO’s mhGAP guidelines and the third edition of the Word Bank’s Disease Control Priorities (DCP3) both recommended that community-based rehabilitations as an adjunct to antipsychotic treatment for schizophrenia [7]. The rehabilitation interventions, which can be implemented by trained community workers, are more needful in low- and middle-income countries due to the shortage of psychiatrists and psychiatric services [8]. These interventions have been proven to be effective and acceptable to address the broader social and livelihood needs of service users in some low- and middle- income countries (LMICs), such as India [9] and Ethiopia [10].

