### Statistical issue

#### Sample size estimation

Based on the data from the earlier random controlled trials [9, 21], it was assumed that the participants in the intervention arm will have 20% reduction on the PANSS total score mean reduction after the 12-months CBR, and there was no change observed for participants in the control arm. The intra-class correlation within the three districts was set at 0.05 and alpha was set as 0.05. Based on methods from previous literature [22], a sample size of 110 participants in both intervention arm control arm was calculated for this trial, which will give us 90% power to detect the difference. The required sample size of 220 was increased to 264 to allow for 20% attrition. The total number of participants will be divided slightly unequally between sub-districts for reasons of feasibility.

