#### Data management and analysis

Data collection and management will follow Good Clinical Practice (GCP) guidelines and Standard Operating Procedure. Each participant will be assigned a unique ID so that their reported data could be identified. Data cleaning will follow standard procedure, and all the changes will be documented. Findings of this trial will be reported according to the revised CONSORT guidelines [23]. Stata 16.0 will be used for quantitative analyses. Data will be password-protected and only accessible for authorized personnel of the research team. In accordance with good trial practices, data and all related documentation will be stored for a minimum of 7 years after the completion of the trial.

All statistical analyses were performed using STATA version 16.0 for Mac (Stata Corp, College Station, TX, USA). Descriptive statistics will be applied to summarize the socio-demographic and clinical characteristics, as well as the outcome measures for all trial participants at baseline, intermediate and endline. Participants who are loss-to-follow-up will be compared using chi-square tests and t tests to assess the potential bias. The primary outcome analysis will be masked until the analyses is finalized and approved by all researchers. Adequate intervention will be defined as having received a minimum of 12 group sessions. We will not define adequate FBC for the control arm a priori. CBR worker’s characteristics such as educational background, post-training competency and relative working experience will also be described.

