Data analysis will be conducted under intention-to-treat assumption. The primary outcome----12-month PANSS total score, adjusted for PANSS scores at baseline and site, and including clustering effects of CBR workers, will be used for examining the comparative effects of intervention and control arm. Personal and social function (PSP score), antipsychotic adherence (MARS score), knowledge of schizophrenia (KAST score) and hospital readmission will be similarly analyzed. A longitudinal analysis including both 6- and 12-month outcomes will also be performed using a GEE or random effects model including an interaction term of time and treatment allowing for modelling changes over time. Long-term outcomes (ADL & IADL, PSSS, EQ-5D, SQLS and BAS score) at 12 months will be analyzed in a similar way to the primary outcome. We will also perform residual analysis to check the data distribution and to detect outliers. Multiple imputation methods will be employed for participants with missing outcome variables.

Several sensitivity analyses are planned to be carried out. First, a complete case analysis and a complier average causal effect will be conducted. Second, a dose-response relationship between adherence to CBR intervention (number of group sessions attended) and the intermediate and long-term outcomes will be examined. Third, we will also conduct data analyses that including received quantity of different CBR modules to identify the active components. Furthermore, regression models will also be re-estimated to include possible confounders such as characteristics of CBR workers and participant characteristics that differ at baseline.

Exploratory subgroup analyses by gender, urban-rural residence, baseline symptom severity and antipsychotic adherence will be completed, although the power for these analyses has not been specifically allowed for.

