#### Cost-effectiveness analysis

Direct costs of the CBR intervention will be estimated by deriving a monetary value based on actual cost. Cost of illness, as the secondary outcome will be computed based on electronic medical records & self-reported data, and then compared at intermediate line and endline. Cost-effectiveness will be assessed by calculating the incremental cost-effectiveness ratios, which will show the extra cost incurred to produce a unit improvement in symptoms, personal and social function, as well as QALYs gained at the endline. To explore the uncertainty around the estimates, cost-effectiveness acceptability curves will be derived to provide the probability of advantages for the FBC combined CBR at a range of ‘willingness to pay’ threshold levels.

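### No listed analysis can show whether the 12-month PANSS result survives dropout that depends on the unseen outcome and differs by arm

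*Protocol article*

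**What the plan says.** All the relevant statements are in the protocol article.

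- **Analysis set** (Data management and analysis): "Data analysis will be conducted under intention-to-treat assumption".
- **Missing outcomes** (same section): "Multiple imputation methods will be employed for participants with missing outcome variables". No missingness assumption is named.
- **Sensitivity analyses** (same section): the list opens with "First, a complete case analysis and a complier average causal effect will be conducted". It goes on to dose-response by sessions attended, quantity of each module received, and models with added confounders.
- **Longitudinal model** (same section): "A longitudinal analysis including both 6- and 12-month outcomes will also be performed using a GEE or random effects model".
- **Check on those lost** (same section): "Participants who are loss-to-follow-up will be compared using chi-square tests and t tests to assess the potential bias". Neither the comparison group nor the arm is mentioned.
- **Expected loss** (Sample size estimation): "The required sample size of 220 was increased to 264 to allow for 20% attrition".
- **Awareness of arm** (Outcome assessment): participants and caregivers will know their allocation at the 6- and 12-month interviews. Only the PANSS and PSP raters are to be blinded.

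**The concern.** A sensitivity analysis for missing data is useful when it changes the assumption that the main analysis cannot verify. Here that assumption is missing at random (MAR): given what was observed, those who left have the same 12-month PANSS distribution as those who stayed. Every listed analysis that bears on missing data keeps this assumption or strengthens it. If CBR dropouts are doing worse than their observed data predict, all of these analyses err in the same direction, and their agreement would look like robustness.

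The design makes arm-specific dropout plausible. Participants know their arm, and only the CBR arm is asked to attend up to 18 group sessions of 90 to 120 minutes (CBR delivery), so reasons for leaving can differ between arms. At stake is whether a positive primary result can be defended against the objection that it depends on how the missing CBR outcomes were filled in.

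**Working it through.** **1. What each planned analysis assumes about missing 12-month PANSS**

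| Planned analysis | Assumption needed | Departs from MAR? |
|---|---|---|
| Multiple imputation, standard form | MAR given the variables in the imputation model | No |
| Complete case, adjusted for baseline PANSS and site | Missingness unrelated to the outcome given arm, baseline PANSS and site only: the same as MAR or stronger | No |
| Random-effects model, months 6 and 12 | MAR given observed outcomes and covariates | No |
| Ordinary GEE, months 6 and 12 | Missing completely at random: stronger | No |
| Complier average causal effect, dose-response, module quantity | Address attendance, not missingness | No |
| Added confounders | Addresses imbalance | No |
| Chi-square and t tests of those lost | Use observed characteristics, so cannot detect dependence on the unseen outcome | No |

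**2. The plan's own attrition figure**

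220 x 1.20 = 264, which reproduces the stated total. If 20% of 264 are lost, 264 x 0.80 = 211 remain, about 106 per arm. If instead exactly 220 of 264 are retained, the missing fraction is 1 - 220/264 = 16.7%. Both fractions are used below.

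**3. Effect of a departure from MAR on the arm difference**

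Let m be the fraction missing in the CBR arm and d the number of PANSS points by which its dropouts are worse than imputed, with no departure in the control arm. The arm mean, and so the arm difference, moves by m x d. The documents give no value for d, so it is assumed over a range.

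| d (assumed) | m = 0.20 | m = 0.167 |
|---|---|---|
| 2 | 0.4 | 0.33 |
| 5 | 1.0 | 0.84 |
| 10 | 2.0 | 1.67 |

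If both arms have the same d but attrition is 25% against 15% (assumed), the shift is (0.25 - 0.15) x d: 0.2, 0.5 and 1.0 points for d of 2, 5 and 10.

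**4. Against the planned effect**

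Sample size estimation assumes a 20% PANSS reduction against no change, but gives no baseline mean. With a baseline of 60 to 80 (assumed), the planned difference is 0.20 x 60 = 12 to 0.20 x 80 = 16 points. A shift of 1 to 2 points is then 1/16 = 6% to 2/12 = 17% of it. Reducing the whole planned effect to zero at m = 0.20 would need d = 12/0.20 = 60 to 16/0.20 = 80 points, which is not credible. An observed difference of 2 points (assumed) would need only 2/0.20 = 10. Statistical significance would be lost at a smaller d than either.

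**The case against.** The strongest reply is that intention to treat with multiple imputation and a complete-case check is conventional and contradicts nothing, that imputation detail usually belongs in an analysis plan, and that the planned effect is too large for a 1 to 2 point shift to overturn. Home visits after three unanswered invitations (Outcome assessment) should also limit loss. Much of this stands. It bounds the importance of the point: a trial that achieves the assumed effect would not be threatened. It does not remove the point, because the article goes beyond silence and lists its sensitivity analyses, none of which departs from MAR, while still expecting 20% attrition.

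Three stronger readings are tempting, and the documents do not support them.

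- **That QALYs will be overstated because deaths are imputed.** A reader might infer this from the unqualified imputation sentence, from "as well as QALYs gained at the endline" under Cost-effectiveness analysis, and from the Background remark that "the mortality rate of people with schizophrenia is two to three times higher than that in the general population". But no section says that deaths will be imputed, the cost-effectiveness section does not invoke imputation, and handling of death is commonly left to an analysis plan. The Background figure is relative and covers all people with schizophrenia, whereas entrants are stable and aged 18 to 59. The size would be small: one mid-year death among 132 at utility 0.75 (assumed) is 0.5 x 0.75 / 132 = 0.0028 QALYs in that arm's mean. The between-arm increment could move either way, or not at all if deaths are equal.
- **That the tests on those lost ignore arm.** The sentence names no comparator, so it fits a between-arm comparison as well as lost against retained. It is unspecified, not wrong.
- **That dropout bias is wholly untested.** Complete case and the comparison of those lost are weak checks, but they are checks. What goes untested is departure from MAR.

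**Conclusion.** The point holds in a limited form. The listed analyses cannot show whether the primary 12-month PANSS result survives outcome-dependent dropout that differs by arm, because each relies on MAR or a stronger assumption. At the plan's 20% attrition, every 5 points by which CBR dropouts are worse than imputed takes 1.0 point off the apparent benefit, and 10 points takes off 2.0. These figures assume a departure in the CBR arm only. The departures and the 60 to 80 point baseline are assumptions, since the article gives neither. The gap is unlikely to matter if the effect is near the planned 20% reduction. It could decide the interpretation if the effect is a few points or borderline. Overstatement of QALYs through imputed deaths is not part of this conclusion.

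**What to change.** 1. Make a delta-adjusted (tipping-point) or control-based multiple imputation of 12-month PANSS the main missing-data sensitivity analysis. In the delta-adjusted form, worsen the imputed CBR values step by step until the conclusion changes, and report that value so readers can judge whether it is plausible. Keep complete case as supplementary.
2. State that the comparison of participants lost to follow-up is made by arm: the proportion lost in each arm, and the baseline characteristics of those lost in each arm.
3. As a clarification only, add that the imputation sentence does not apply to participants who died.

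The cost is revised analysis wording and a few extra runs in the Stata version already named, on outcome data already being collected. The downside is that the robustness statement may look less favourable.

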#### Allocation

The randomization processes of sub-districts to intervention and control arms are as follows: (1) The sociodemographic characteristics and specific information of patients with schizophrenia of each sub-district will be obtained from the information system [11]; (2) A pairwise matching work will be conducted to identify 9 pairs of matched sub-district that share similar characteristics (number of population, prevalence of schizophrenia, average income per capita, etc.); (3) Within each pair, one sub-district will be randomly assigned into intervention arm, and the remaining one will be assigned into control arm, yielding to 9 sub-districts in intervention arm that providing FBC + CBR, and 9 sub-districts in control arm with FBC only. The sub-district allocation list will be kept securely on a password-protected document by the trial coordinator. To reduce selection bias, the potential eligible participants will not be informed about the allocation of their sub-district until they have consented to participate and baseline data of all participants have been collected. Recruitment and participant flow will be closely monitored by the trial coordinator.

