##### CBR worker recruitment and training

Nineteen CBR workers were recruited from mental health center of the three districts in Weifang city according to the following criteria: (1) at least 12 years of schooling, (2) resident in Weifang city, (3) one-year-or-above working experience related to psychiatry or psychology and (4) interest in community work. CBR training was delivered by multiple sessions at different time (time before delivering new module) to ensure that each intervention module was fully learned and will be smoothly implemented. A intervention manual will be provided for each CBR worker. The competency of CBR workers will then be assessed using role-plays and patient vignettes.

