##### CBR delivery

The CBR intervention will be delivered by group at community health centers. Two CBR workers will be attached to each sub-district and have one group of 10–20 people with schizophrenia. CBR delivery will commence immediately after recruitment into the trial. A total of 18 group intervention sessions will be implemented within the following 12 months, and each group intervention session will last 90–120 min. The intervention is delivered in two phases (Table 1): In phase 1 (intensive engagement phase), 12 intervention sessions will be delivered fortnightly during the first 6 months. The content of the intervention includes a series of modules such as developing a positive therapeutic alliance, understanding schizophrenia, adherence management, etc. (Table 1). In phase 2 (stabilizing phase), 6 intervention sessions will be delivered monthly during the last 6 months. Intervention modules in this phase are similar with phase 1 to reinforce the progress, and the content will include more in-depth discussion and address unmet needs from the first phase. In this phase, a personal rehabilitation plan for each participant will be generated to help their continued rehabilitation at home.

The content and process of the phase specific delivery of the intervention has been manualized. CBR workers will be closely supervised at each site by psychiatrists who will work as designated intervention coordinators. They will coordinate the overall delivery of the intervention and assure the quality and fidelity of the intervention at the site. The treating psychiatrists will provide clinical leadership for the community care teams and ongoing supervision to maintain safety and quality standards.

In total, we anticipate that each participant in the intervention arm will receive a maximum of 18 group-based rehabilitation sessions during the 12 months of the intervention. In evaluating the intervention, a minimum adequate number of 12 sessions attended over 12 months was set according to priori definitions.

**Table 1 Tab1:** CRISC community-based rehabilitation (CBR) intervention outline

phase	months	frequency	Objectives	CBR Modules	CBR activity

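### One sensitivity analysis adds CBR-worker characteristics as confounders, but these exist only in the intervention arm, so in a two-arm model the arm effect is lost or shifted unless the terms are centred within that arm

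*Protocol article*

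**What the plan says.** The section on data management and analysis fixes the primary 12-month PANSS model as "adjusted for PANSS scores at baseline and site, and including clustering effects of CBR workers". The other outcomes are to be analysed in a similar way.

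A later paragraph of the same section opens with "Several sensitivity analyses are planned to be carried out". It lists a complete case analysis, a complier average causal effect, a dose-response analysis by sessions attended, and an analysis by quantity of each CBR module received. It then adds that "regression models will also be re-estimated to include possible confounders", and describes the added covariates as "possible confounders such as characteristics of CBR workers and participant characteristics that differ at baseline". The sentence does not say which regression models are meant, or what value a control participant takes on a worker variable.

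Earlier in the section, the worker characteristics to be described are education, competency after training and working experience. On who has a CBR worker, three places matter:

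- Allocation: "9 sub-districts in control arm with FBC only".
- CBR worker recruitment and training: "Nineteen CBR workers were recruited from mental health center of the three districts in Weifang city".
- CBR delivery: "Two CBR workers will be attached to each sub-district and have one group of 10–20 people with schizophrenia".

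**The concern.** A confounder of a randomised comparison would have to be a characteristic that both arms possess and that does not result from allocation. The education, competency and experience of the person who delivers CBR are attributes of the intervention. A control participant has no such person, and competency after CBR training has no counterpart in usual care.

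A sensitivity analysis is read as a test of the main result. If this one fails to fit, or silently estimates a different quantity, a real benefit may look fragile, or agreement between the two models may be given weight that it does not deserve.

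The second half of the sentence raises a smaller matter. If participant covariates are chosen because they happen to differ at baseline, the model is not settled until the data have been seen, and the choice rests on chance imbalance and not on prognosis.

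**Working it through.** The protocol gives no figure on this point, so there is none to reproduce. The check has four steps.

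**1. Do worker characteristics exist for controls?** Two workers per sub-district in the 9 intervention sub-districts need 2 × 9 = 18 workers. All 18 sub-districts would need 2 × 18 = 36. The 19 recruited cover the first and not the second. With controls receiving FBC only, the variables are defined in the intervention arm alone.

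**2. Control values left missing.** A complete-case fit drops every control. Arm is then constant and identical to the intercept. The design matrix (intercept, arm, worker variable) has rank 2 of 3, so the arm effect cannot be estimated.

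**3. Controls coded zero.** Let the effect in a sub-district whose worker value is w be d + b(w − w̄), where w̄ is the mean worker value, d the average effect and b the slope. With uncentred w and controls at 0, the arm coefficient estimates d − b·w̄, the effect at w = 0. Recruitment required at least one year of relevant experience and 12 years of schooling, so zero lies outside the range of both.

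Inputs for illustration:
- From the protocol: 9 + 9 sub-districts; ICC 0.05, which the protocol attaches to districts and which is applied here to sub-districts; 12 participants per sub-district (220/18 = 12.2).
- Assumed: total SD 1 before any worker effect; one worker value per sub-district with mean 5 and SD 2; d = 0.5 SD; b = 0 or 0.1 SD per unit.

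Expected arm coefficient with b = 0.1: 0.5 − 0.1 × 5 = 0.

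Standard errors with b = 0:
- Variance of a sub-district mean: 0.05 + 0.95/12 = 0.129.
- Unadjusted: √(2 × 0.129/9) = 0.17.
- Zero coding adds the variance of b̂·w̄. This is 0.129 × (25 + 4/9)/(4 × 6) = 0.137, where 6 = 8 − 2 comes from the expected inverse of a chi-square on 8 degrees of freedom. The total is 0.0287 + 0.137 = 0.166, so the SE is 0.41.

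Simulation (4,000 runs per scenario, true average effect 0.50), mean estimate (SE):

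| Model | b = 0 | b = 0.1 |
|---|---|---|
| No worker term | 0.50 (0.17) | 0.50 (0.18) |
| Worker term, controls coded 0 | 0.49 (0.41) | 0.00 (0.41) |
| Worker term centred in intervention arm, controls 0 | 0.50 (0.17) | 0.50 (0.18) |

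Centring repairs the arm coefficient. It also shows that the term then leaves the arm estimate where it was: it describes variation within the intervention arm and removes no confounding.

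**4. Participant covariates chosen on imbalance.** The same set-up was used with six baseline covariates, jointly correlated 0.5 with outcome. Each was adjusted for only if its baseline t test gave p < 0.05 (an assumed rule). At least one was selected in about 27% of trials (expected 1 − 0.95⁶ = 26.5%). The arm effect averaged 0.50, with SE 0.17 for b = 0 and 0.18 for b = 0.1. With no true effect, the type I error was 5.1%, against 5.4% unadjusted.

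**The case against.** The strongest reply is that the sentence may concern only models within the intervention arm. The dose-response and module analyses come immediately before it. There worker experience and competency are defined and could confound the link between attendance and outcome. That reading is possible, but it is not what the text says. The sentence starts a further item, refers to regression models without restriction, and pairs worker traits with participant characteristics that differ at baseline, which most naturally means differ between arms. If the narrower meaning was intended, saying so costs a few words.

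A second reply is that the coding of a sensitivity covariate is ordinary SAP detail, and that one coding, centring, works. Both statements are true, so failure is not inevitable. What does not belong to the SAP is the label: the protocol itself names these variables as possible confounders, which they cannot be for the arm comparison.

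Three stronger readings are tempting and are not supported:

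- A reader might infer that the adjusted between-arm results in general are compromised. The primary model adjusts for baseline PANSS and site, with workers entering as a clustering effect. Worker characteristics are not among its covariates, and the other outcomes follow the same pattern.
- A reader might infer that choosing covariates on imbalance also makes the arm effect uninterpretable. Step 4 showed no bias and no inflation of the type I error under its assumptions.
- A reader might wish to state how often balanced covariates would be flagged by tests that ignore clustering. The protocol names no test for baseline differences and no ICC for the covariates, and it matches sub-districts in pairs, so no such figure can be drawn from it.

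**Conclusion.** The point holds for one sensitivity analysis. CBR-worker characteristics are features of the treatment and are undefined in controls. In a two-arm model with these terms the arm effect is not estimable with controls missing, or refers to an arbitrary worker value with controls coded zero, unless the terms are centred within the intervention arm. The loss of rank follows from the design alone. The shift from 0.50 to 0.00 and the rise in SE from 0.17 to 0.41 depend on the assumed worker mean, spread and slope; they show the mechanism and do not predict this trial's result.

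Selecting participant covariates because they differ at baseline is a separate and lesser weakness of pre-specification. The conclusion of the primary analysis does not depend on either matter.

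**What to change.** Change two pieces of wording in the sensitivity analysis paragraph:

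1. State that CBR-worker characteristics are used only in analyses within the intervention arm, such as dose-response and modules. If they are kept in a two-arm model, state that they are centred within the intervention arm with controls set to 0. Do not call them confounders of the arm comparison.
2. Replace the participant characteristics that differ at baseline with a short list of prognostic covariates already collected (for example age, sex, illness duration and baseline MARS). Fix the list before unmasking and use it with sub-district clustering.

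No new data are needed and the primary analysis is unchanged. The downside is that a chance imbalance in a variable not on the list would be handled only in a further model labelled post hoc.
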